### Experimental Group: Exercise-Based Aquatherapy

In addition to conventional physiotherapy, participants randomized to the experimental group, which involves aquatherapy, will receive a 45-minute exercise session delivered by the physiotherapist in the aquatic machine thrice weekly for 4 weeks. The exercises include aerobic training, psychosocial developmental well-being, and resistance training guided by published recommendations [7,14,15]. These exercise sessions will be individually tailored and include a waterjet in the aqua machine for resistance, treadmill walking in the aqua machine, balance activities, aerobic training, and functional activities. All these exercises, which are part of endurance training, will be conducted within the aquatherapy machine itself, involving mild to moderate aerobic exercises (eg, slow paced treadmill walking in the aqua machine, water-splashing activity, spot marching, and sidestepping). The aquatherapy machine also has grab bars and a seat for exercises that work on improving balance. The therapist will choose exercise variations, for example, upper-limb strengthening by using weights or lower-limb strengthening by using the waterjet provided in the aqua machine. Initial warm-up exercises include various upper- and lower-body stretches and balance exercises. Water-splashing activities with play therapy is included to improve psychosocial well-being. Exercise intensity will depend on verbal feedback from the participant, observation by the physiotherapist, and as per standard protocol-based intensity. Resistance exercise will involve, first, active-assisted range of motions followed by active range of motions. To improve balance, aqua-plyometric exercises will also be done in the aqua machine under the physiotherapist’s guidance. Before starting the exercises, aerobic training as a warm-up for 5 minutes will be followed by a cool-down for 5 minutes (Table 1).

The participants will receive an overview of the exercise regimen and study protocols linked to rehabilitation from the physiotherapist who will be evaluating and administering the aquatherapy intervention. The sessions will be for 45 minutes each, with 3 sessions per week for 4 weeks [10,11]. Activities are aimed at improving motor function and psychosocial well-being. The fidelity of the intervention will be monitored by recording the content of the exercise session and duration of the completed sessions. Participants in both groups will also be asked whether they received any exercise-based intervention outside of the trial at the 4-week assessment and follow-up.

**Table 1 table1:** Intervention and comparison group descriptions based on the TIDieR (Template for Intervention Description and Replication) checklist.

	Experimental group	Comparison group
In brief	Aquatherapy rehabilitation	Conventional physiotherapy
Why	Exercise intervention in the aquatherapy machine is safe, effective, and convenient to use for improving the quality of life of individuals with ALL undergoing chemotherapy.	Individuals with ALL undergoing chemotherapy are routinely offered rehabilitation.
What (materials)	Preparations before the aquatherapy session: Avoid a heavy meal before the session Remain well hydrated before the session Maintain water temperature Wear proper clothing before entering the aquatherapy machine Follow general principles for duration, frequency, and intensity to be maintained Provide participant with weight cuff Aquatic therapy machine equipped with an underwater treadmill and adjustable resistance jets	Rehabilitation is delivered using standard physiotherapy techniques without the use of any specialized equipment Rehabilitation focuses on land-based exercises
What (procedures and heath care provider)	Physiotherapist will provide aquatherapy session protocol in written format	Physiotherapist will provide the exercise guidelines
How	Supervised session in aquatherapy machine Digitally controlled aqua machine allows for real-time monitoring of water speed and session duration, ensuring consistency in exercise intensity.	In person
Where	Aquatherapy machine is placed in the pediatric outpatient department Participants receive aquatherapy in the pediatric outpatient department	Participants receive conventional physiotherapy in the hospital (inpatient department) itself
When and how much (intensity)	Warm up: stretching 30 s, hold, 3 repetitions Aerobic exercises: underwater treadmill walking with minimum speed Strengthening exercises: 10 repetitions, 2 sets Resistance exercises: 10 repetitions, 2 sets Balance exercises: 5 s, hold single leg stance, and progress up to 10 s holds	Fatigue: Jacobson relaxation exercise and aerobic exercises like walking Strengthening exercises: 10 repetitions, 3 sets Resistance exercises: 10 repetitions, 2 sets Balance exercises – 5 s hold single leg stance and then progress up to 10 s holds (eg, heel walking, toe walking, with eyes open and eyes closed)
Frequency	3 sessions per wk, supervised	5 sessions per wk, supervised
Session time	45 min	45 min
Overall duration	4 wk	4 wk
Tailoring	Exercise is tailored to each participant’s ability	Exercise is tailored to each participant’s ability
Trial fidelity	Physiotherapist Intervention will be delivered as planned Ensuring all participants receive the intervention in the same way	Physiotherapist Intervention will be delivered as planned Ensuring all participants receive the intervention in the same way

### Study Outcomes

Participants will be assessed at weeks 0, 4, and 12. The primary end point is immediately after the intervention (week 4). Physical activity, balance, and psychosocial well-being will be assessed at weeks 0 and 4. Primary and secondary outcomes are as outlined in Table 2.

**Table 2 table2:** Primary and secondary outcomes, measures, and time points of the intervention.

Outcomes	Measures or sources	Definitions	Time points
Primary outcome: balance	Pediatric Balance Scale [16]; reliability 0.97	This 14-item scale is simple to administer, does not require any specialized equipment. Performance can be measured both quantitatively and qualitatively using a 0 to 4 grading system.	Wk 0; wk 4
Functional mobility	Timed up and go test [1,17]; reliability (ICC>0.80)	The test evaluates functional mobility and balance by timing how long it takes a participant to get up from a seated posture, walk 3 min, turn around, go back, and sit down. <10 s—typical mobility; 10-14 s—independent walking but modest motor deficits. >20 s—severe restrictions with higher risk of fall; 15-20 s—intermediate mobility issues, requiring some assistance	Wk 0; wk 4
Secondary outcome: motor function	Functional Independence Measure for Children (WeeFIM) [18,19]	A popular instrument for evaluating the functional capacities of individuals undergoing rehabilitation, the functional independence measure focuses on independence in everyday activities. Each of the 18 items in the FIM is scored on a scale of 1–7, with higher scores indicative of greater independence. The items are separated into motor and cognitive categories. Development and rehabilitation requirements of individuals can be inferred from their overall score, which ranges from 18 (total reliance) to 126 (full independence).	Wk 0; wk 4
Psychosocial well-being	Hospital Anxiety and Depression Scale (supplementary file [18])	It is a 14-item questionnaire used in hospital settings to measure sadness and anxiety. Each of the two subscales (depression and anxiety) has 7 items and is scored between 0 and 3, with a maximum score of 21 per subscale; 0-7 (normal), 8-10 (mild), 11-15 (moderate), and 16-21 (severe) are the interpretations for the scores. The HADS^a^ is a useful instrument for early detection and monitoring of mental health issues in individuals receiving therapy because a score above 8 suggests substantial symptoms.	Wk 0; wk 4

^a^HADS: Hospital Anxiety and Depression Scale.

“Adverse events,” as defined by the World Health Organization [19], will be recorded from medical records, direct observation during classes, and by participants’ self-reporting to document the safety of the intervention. The event may or may not be related to the intervention but may occur while the individual is participating in the intervention phase of the trial. Adverse events will be categorized as minor or serious, related or unrelated, and expected or unexpected. A minor adverse event is defined as an incident that occurs during the intervention but results in no injury or minor injury requiring no or minor medical intervention. A serious adverse event is defined as an incident that occurs during the intervention, resulting in death, serious injury, or hospitalization (eg, injurious fall resulting in fracture). Serious adverse events will also be recorded for the usual care group. In addition, adverse events will be reported and graded using the Common Terminology Criteria for Adverse Events Version 4 [20]. The consequences of a serious adverse event in the control group (eg, hospitalization and emergency-department admission) will be captured by the health service utilization questionnaire and medical record audit. Reasons for nonparticipation in an exercise session or noncompletion of the program will also be recorded (eg, pain, fatigue, and feeling unwell).

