## Introduction

Acute lymphoblastic leukemia (ALL) is one of the most common cancers affecting children, with about 64,200 cases reported worldwide. In India, the highest incidence occurs among children aged 2–5 years, with rates of approximately 101.4 cases per million boys and 62.3 cases per million girls [1]. The availability of more advanced therapeutic agents, enhanced supportive care, therapy stratification, and regimen modification in recent times has led to a cure rate of more than 80% and an overall survival probability of 80% to 90%. As a result, awareness about therapy-related morbidity has increased because of the longer survival rates [1].

Acute chemotherapy comprises 2 phases: the induction phase and the consolidation phase. The primary goal of the induction phase is remission. Intense chemotherapy is used during this phase, which typically lasts 4 weeks, to destroy as many leukemia cells as possible. After a successful induction therapy session, patients are moved into the consolidation phase, sometimes referred to as intensification. This phase is aimed at eradicating any leukemia cells that could have remained unaffected during the induction phase. Additional chemotherapy regimens that are different from those used in induction are part of the consolidation phase, which usually lasts many months. This is the most intense phase, requiring a prolonged hospital stay. Children with ALL are considerably less active during the acute stage, usually presenting with deficits in fatigue and activity tolerance [2,3]. They may also exhibit motor deficits as a side effect of the chemotherapy drugs, which include anthracyclines and vincristine. While anthracycline-induced cardiotoxicity reduces aerobic capacity, vincristine-induced neuropathy impairs peripheral sensory and motor function [4,5]. Chemotherapeutic drugs such as vincristine have an adverse effect on balance, which may occur through diverse mechanisms such as by decreasing muscular strength and flexibility or producing cognitive impairment [1]. When used on children with ALL, these drugs can result in self-imposed or medically prescribed activity restrictions, which would lead to routinely engaging in lesser physical activity [1,6].

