### Inclusion and Exclusion Criteria

Participants who are aged 4 to 18 years [1], have ALL, and are undergoing acute stages of chemotherapy treatment can be included. The children must be ambulatory, can be of either sex, and must be in the induction or consolidation phase of chemotherapy for ALL.

Children (1) who are medically unfit to participate in the exercise session as determined by a physiotherapist or medical practitioner considering published recommendations [13]; (2) who have discontinued chemotherapy; (3) who have been diagnosed with sepsis; (4) who have preexisting cardiovascular disease, acute or chronic respiratory disease, acute or chronic bone, joint, or muscular disorders, neuromotor deficits or genetic disorders; and (5) with auditory or visual impairments are excluded from the trial.

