### Participant Safety and Ethical Considerations

The quality of the water will be routinely observed and recorded. Until medically cleared, children with open wounds, central lines, or symptoms of skin infections will not be allowed to participate in aquatherapy. Before each session, a pediatric oncologist will check all participants for symptoms of fever or active infections. For emotional support during the first sessions, parents or other caregivers may be present. The research ethics board will be notified of all adverse events, mild or major. Before participating, families will be briefed on any possible dangers and asked to sign a form providing informed consent and assent. Periodically, a data safety monitoring team will examine events and make necessary protocol adjustments.

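### Participant self-report is a named adverse-event source from age 4 with no caregiver reporter, so minor events between sessions may be missed in the youngest children

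*Protocol article*

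**What the plan says.** In the protocol article, Study Outcomes states that adverse events "will be recorded from medical records, direct observation during classes", and also "by participants’ self-reporting to document the safety of the intervention". Inclusion and Exclusion Criteria admits "Participants who are aged 4 to 18 years".

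Study Outcomes describes the time window in two ways. Events in general "may occur while the individual is participating in the intervention phase of the trial". The definition of a minor event is narrower in wording: "A minor adverse event is defined as an incident that occurs during the intervention". The same section says that serious events are also recorded in the usual care group, presumably the comparison arm. It makes no matching statement about minor events there.

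Parents and caregivers appear in three roles, none of which is reporting events. They consent and may ask questions (Patient Selection and Consent). Families are briefed on possible dangers (Participant Safety and Ethical Considerations). And in that same section: "For emotional support during the first sessions, parents or other caregivers may be present".

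**The concern.** Self-report alongside chart review and observation is a usual arrangement in adult exercise trials. It fits less well at the lower end of an age range that starts at 4. A child of that age may not volunteer a fall, next-day soreness, skin irritation or unusual tiredness, or may not link it to an earlier session. The person most likely to notice is the caregiver, whom the article does not name as a source.

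The stated purpose of these data is to document safety. Participant Safety and Ethical Considerations sends all events, whatever their severity, to the ethics board and has a monitoring team review events and adjust the protocol where needed. If minor events go unrecorded in the least verbal children, both bodies see a lower absolute count than actually occurred.

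**Working it through.** **1. Which route would catch which event.** The routes that the article names, set against a minor event between sessions:

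| Route | Section | Catches the event if |
|---|---|---|
| Medical records | Study Outcomes | it leads to a chart entry |
| Observation during classes | Study Outcomes | it occurs, or still shows, in a session |
| Reasons for missed sessions or noncompletion | Study Outcomes | it stops attendance |
| Pre-session oncologist check | Participant Safety and Ethical Considerations | it shows as fever or active infection |
| Health service utilization questionnaire and record audit | Study Outcomes | it is a consequence of a serious event in the control group |
| Participant self-report | Study Outcomes | the child reports it |

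The pre-session check is worded as "Before each session, a pediatric oncologist will check all participants for symptoms of fever or active infections". What remains is a minor event outside sessions, with no chart entry, no missed session, no fever or infection, and nothing visible at the next class. For that group, self-report is the only named route.

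**2. Whether such events are in scope.** Read as sessions only, the minor-event definition would exclude them, whoever reported them. Read with the sentence on the intervention phase, it includes them. Self-report is listed separately from observation in class, which makes most sense if events outside class count, but the text does not settle it.

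**3. How large the loss could be.** The only input from the article is the arm size. Its formula in Sample Size Estimation reproduces: 2 × (1.96 + 1.64)² / (1.12 / 1.09)² = 24.55; 1.96² / 2 = 1.92; the sum is 26.47, rounded up to 27 per group. This serves here only as a head count.

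Lost events per arm = 27 × f × m × (c₁ − c₀), where all four inputs are assumptions:

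- f, the share of children under 8: 0.40 to 0.50, that is 27 × 0.40 = 10.8 to 27 × 0.50 = 13.5 children.
- m, such events per child over 4 weeks: 0.1 to 1.
- c₀, capture by the child alone: 0.30 to 0.60.
- c₁, capture with a caregiver: 0.80, so c₁ − c₀ runs from 0.20 to 0.50.

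Low end: 10.8 × 0.1 × 0.20 = 0.2. With one event per child: 10.8 × 1 × 0.20 = 2.2 to 13.5 × 1 × 0.50 = 6.75.

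The range of 0.2 to 6.75 spans a factor of about 31 (6.75 / 0.216). It reflects the assumptions, so it is not an estimate. The figure is zero for an arm in which minor events are not collected at all.

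**The case against.** The strongest reply is that a journal article condenses the full protocol. How reports are elicited, how often, and who speaks for a small child usually sit in the full protocol or the case report form, and naming self-report does not forbid a parent to speak. That stands for the mechanics of elicitation, whose absence is no fault. It does not fully answer the point, because the article does state who reports, and that statement fits the youngest eligible children poorly.

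Several stronger readings are tempting, and the objections to them hold:

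- *Minor harms will be under-recorded.* Sessions are supervised 3 or 5 times a week (Table 1), each child is checked beforehand, symptoms of skin infection bar a child from aquatherapy until cleared, and pain or fatigue that stops attendance is recorded. Only *may be* is supported.
- *The missed events are events at home.* The Introduction describes a prolonged hospital stay, and Table 1 places the comparison treatment in the inpatient department. Events in inpatients could reach the chart. The defensible term is outside sessions.
- *The sample will be mostly very young.* The Introduction says "the highest incidence occurs among children aged 2–5 years", but only ages 4 and 5 of that band are eligible, and the trial's expected age distribution is not given. The point needs only that some young children enrol.
- *Aquatherapy will look safer than the comparator.* Randomization should spread age-dependent under-reporting over both arms. Table 1 gives aquatherapy in the outpatient department, and if those children also lived at home, chart capture could differ by arm. But the table says where treatment is given, not where children stay. Any uneven collection of minor events would be a separate problem.
- *Caregivers figure only as emotional support.* They also consent and are briefed on risks.

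**Conclusion.** The point holds in a limited form. The named sources include self-report from age 4 and no caregiver report, so minor events outside sessions that leave no record and do not stop attendance may be missed in the youngest children. The effect would be to understate absolute harm. This rests on two assumptions: that some children of about 4 to 7 enrol, and that events between sessions are in scope.

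The size cannot be estimated from the article. A reader might infer a definite loss of, say, 2 to 7 events per arm, but that needs one event per child and capture rates found nowhere in the document. No primary or secondary outcome, analysis or sample size depends on this point. It is worth correcting because the affected data are the trial's record of safety and the correction is cheap.

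**What to change.** In Study Outcomes:

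1. Replace participants' self-reporting with *participant or caregiver report*. Collect it with the same short checklist on a fixed weekly schedule in both arms through week 4, and record who answered.
2. State that minor as well as serious events are collected in both arms.
3. Reconcile the minor-event definition with the sentence on the intervention phase, so that events between sessions count.

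The cost is a few minutes per child per week and one form field for the respondent. Parents are already involved through consent. The small downside is that more minor events will be recorded. If the full protocol already provides for caregiver report, one added phrase in the article closes the first item.

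### The serious adverse event definition omits life-threatening events and prolonged hospitalization, so a severe, survived event in a child already admitted may be labelled minor or fit neither class

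*Protocol article*

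**What the plan says.** All statements are in the protocol article.

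- Study Outcomes, adverse-event paragraph, sets a two-level scale: "Adverse events will be categorized as minor or serious". The other two splits in that sentence, on relatedness and expectedness, do not bear on this point.
- The same paragraph defines the upper level: "A serious adverse event is defined as an incident that occurs during the intervention, resulting in death, serious injury, or hospitalization". With its example, a fall with a fracture, the list of outcomes reads "resulting in death, serious injury, or hospitalization (eg, injurious fall resulting in fracture".
- It defines the lower level as an incident during the intervention that "results in no injury or minor injury requiring no or minor medical intervention".
- It adds CTCAE version 4 grading, without tying any grade to the serious class.
- Inclusion and Exclusion Criteria: children "must be in the induction or consolidation phase of chemotherapy for ALL".
- Introduction, directly after describing consolidation: "This is the most intense phase, requiring a prolonged hospital stay".
- Table 1, row on where treatment is given, comparison group: "Participants receive conventional physiotherapy in the hospital (inpatient department) itself". Experimental group: "Participants receive aquatherapy in the pediatric outpatient department".
- Participant Safety and Ethical Considerations: every adverse event, whatever its severity, goes to the research ethics board, and a data safety monitoring team reviews events periodically.
- Abstract, Methods: length of stay, readmissions and emergency department presentations are recorded as health service data.

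Neither a life-threatening event nor prolongation of an existing admission appears as a seriousness criterion anywhere in the article.

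**The concern.** The definition is written out in full as a closed list of three outcomes, so this is not a detail that a condensed article has left to a longer document. Two of the three outcomes are death and injury. The third, hospitalization, is the only one that would normally pick up a severe but survived medical event such as an infection or drug toxicity. It works only for a child who is at home when the event starts. In this population, some children will already be in hospital.

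The hazards that the protocol itself guards against are largely infectious: it monitors water quality, holds back children with open wounds, central lines or skin infection, and screens for fever before each session. Yet both event classes are worded around injury.

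The count of serious events is the figure that readers of a safety report look at first. If severe inpatient events are missing from it, or sit among the minor ones, the count understates harm in a vulnerable group, and the monitoring team sees those events without the label that would mark them out.

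**Working it through.** No arithmetic applies: the point concerns the wording of a definition, and the plan gives no figure to reproduce. The check applies the two definitions literally to one case: a child already admitted for chemotherapy who, during the intervention period, has a life-threatening infection or toxicity, survives it, and stays in hospital longer as a result.

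**Step 1: the serious criteria, one by one.**

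| Criterion in Study Outcomes | Met by this case? |
|---|---|
| Death | No; the child survives. |
| Serious injury | Not on the ordinary meaning. The term is undefined and its example is a fracture. An assessor could stretch it to cover organ damage or sepsis, but nothing in the text says so. |
| Hospitalization | No; the child is already in hospital. It would be met only if the child were discharged and then readmitted because of the event. |

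Read literally, no criterion is met.

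**Step 2: the minor definition.** Its wording can be parsed in two ways.

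- If the clause on medical intervention governs the whole phrase, the event is not minor, because it needed major medical intervention. It then fits neither class, and the two-level scale is not exhaustive.
- If that clause attaches only to minor injury, an event without injury is minor whatever treatment it needed. A life-threatening infection is then labelled minor.

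Neither parse gives the right label.

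**Step 3: does the setting make such a case realistic?** Eligibility is limited to induction and consolidation. The Introduction describes a prolonged stay in the most intense phase, and Table 1 gives the comparator in the inpatient department. The article does not say that every child is admitted throughout, but it plainly expects inpatients among the participants.

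**Step 4: does another provision repair the label?**

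- CTCAE grading records severity. No grade is linked to the serious class, so a high grade does not move an event into it.
- Notification to the ethics board covers all events. It ensures that the event is seen, not that it is counted as serious.
- Length of stay is collected as a health service measure and is not a seriousness criterion.

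These provisions preserve the information. None of them changes the classification.

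**The case against.** The strongest reply is that little is lost. Events are drawn from medical records, observation and self-report, graded by CTCAE, sent without exception to the ethics board and reviewed by a monitoring team, and length of stay is recorded. All of that stands, and it limits the point to labelling. It does not answer it, because the serious event count is built from the label.

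A second reply is that an assessor could call a septic deterioration a serious injury, and that a readmission would count. That also stands: it would be too strong to say that a severe inpatient event can never be serious. But a definition that depends on how each assessor reads an undefined term will be applied inconsistently.

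Two stronger readings are tempting, and the article does not support them.

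- **Bias between the arms.** A reader might infer from Table 1 that comparator children are inpatients and aquatherapy children outpatients, so that the same event would count in one arm only. Table 1 gives the place of the session, not the child's admission status. Allocation is randomized, and recruitment is from a single hospital. The Experimental Group section describes aquatherapy as given on top of conventional physiotherapy, although the Intervention section suggests otherwise. Study Outcomes names hospitalization and emergency admission as possible consequences of serious events in the control group, so control children are evidently not expected to be in hospital throughout. Bias would arise only if admission status differs by arm, and the article does not state that it does.
- **Over-counting of planned admissions.** A reader might infer that a scheduled chemotherapy admission meets the hospitalization criterion. The definition requires an incident that results in hospitalization, and a scheduled admission does not result from an incident.

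**Conclusion.** The point holds as a fault of classification. The article fixes a closed seriousness rule that lacks two criteria needed in a population that includes inpatients, and a minor class that does not cover the remainder. Severe, survived medical events in children already admitted will tend to be under-classified, and the serious event count will be too low to that extent.

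The size cannot be given as a number. It depends on how many children are admitted when an event occurs and on how often severe non-fatal events occur, and the article reports neither. If few children are inpatients during the intervention, the effect is small; if most are, the hospitalization criterion does little work.

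The conclusion rests on two assumptions: that the definitions are applied as written, and that some participants are in hospital during the intervention, as the Introduction and Table 1 indicate. It does not depend on any difference between the arms. It affects neither the efficacy analysis nor the capture of events. It should be corrected before recruitment, because re-coding events afterwards is less clean than coding them correctly the first time.

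**What to change.** Change the adverse-event paragraph under Study Outcomes and the adverse event form in two places:

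1. Add two criteria to the serious definition: the event is life-threatening, or it prolongs an existing hospitalization. Keep death, serious injury and hospitalization as they are.
2. Define a minor adverse event as every adverse event that is not serious, so that the two classes cover all events and do not overlap. Let the CTCAE grade already planned carry the information on severity.

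The cost is about two sentences of text and an edit to the form. No additional data collection is needed, since medical records and length of stay are already sources. The one small downside is that more events will be reported as serious.
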